### Outcome Measures

#### Primary Outcomes

The primary outcomes of this study are the feasibility of the proposed protocol, the dose of unsupervised robot-assisted therapy performed by participants, and the difference between usability and user experience between the phases where a therapist is present (ie, supervised and minimally supervised phases) and the unsupervised phase.

Feasibility is measured as the number of patients who could transition to the unsupervised phase out of the total number of tested patients, attendance during the unsupervised phase, and safety of use. Attendance is defined as the percentage of days out of the total number of offered days where the patient trains with the device at least once, while safety is defined as the number of adverse events and device deficiencies throughout the entire protocol.

The different metrics used to characterize therapy dose are therapy duration in minutes, number of task repetitions (ie, the number of target movements performed), and percentage change in physical therapy time with respect to the conventional therapy program. Total conventional physical therapy time is estimated from the sum of the duration in minutes of the physiotherapy (without differentiating between upper limb and lower limb) and occupational therapy sessions regularly performed by each patient at the clinic.

Platform usability is assessed with the System Usability Scale [29], the raw Task Load Index [30], and the Post-Study System Usability Questionnaire [31]. User experience during robot-assisted therapy is assessed with the Net Promoter Score [32] and the Customer Satisfaction Score, as well as by evaluating the reasons (if any) for not attending the therapy sessions with the device.

The results of the checklist used to define which patient can proceed to unsupervised therapy are also used to identify specific aspects of the platform that might need to be further improved.

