#### Secondary Outcomes

The difference in intensity (ie, number of task repetitions per minute) and task performance during supervised or minimally supervised therapy and unsupervised therapy is used to evaluate if the content of the therapy varies when the therapist is no longer present. A task repetition corresponds to the target action that the patient must perform in a given exercise (eg, a movement or combination of movements, such as one opening and closing of the hand or interacting with one virtual object rendered by the robot). A third metric to evaluate the difference in therapy content is the ratio of effective therapy time (ie, net therapy time without breaks) to total duration of a therapy session during supervised or minimally supervised therapy and unsupervised therapy.

Functional recovery, assessed as the difference between the baseline and final scores in the clinical and robotic assessments, is another secondary outcome. Clinical assessments comprise the Fugl-Meyer Assessment for upper extremities [33], ABILHAND [34], the Box and Block Test [35], the Motor Evaluation Scale for Upper Extremities in Stroke Patients [36], and the modified Ashworth Scale [20]. Robotic assessments comprise active range of motion, hand proprioception, and haptic perception (A1-A3 in [25]).

The scores of the cognitive assessments performed during the screening visit (Goodglass-Kaplan scale and levels of cognitive functioning-revised) are used to gain more insights into the effect of cognitive function on the ability to transition to the unsupervised phase.

Other parameters possibly influencing therapy dose or attendance are also evaluated. These comprise age, baseline assessment scores, functional recovery, the number of total conventional therapy sessions, and functional independence and mobility, as assessed with the Barthel index [37] and custom questions every time the checklist is performed (ie, at the end of each week of minimally supervised therapy).

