### Data Analysis

Descriptive statistics will be used to describe the study population (eg, demographics, initial clinical scores, and changes in clinical scores, such as functional recovery), attendance and therapy dose in the unsupervised phase, user experience, and platform usability.

Normal distribution of the data will be checked with the Shapiro Wilk test. For each usability metric, a paired *t* test (normal distribution) or a paired samples Wilcoxon test (for data not normally distributed) will be performed to compare the data collected during the usability evaluation 1 and usability evaluation 2 sessions.

To evaluate the content of unsupervised therapy, 1-way repeated measures ANOVA or its nonparametric version (Friedman test) with post hoc tests will be run to compare intensity (average block intensity for each patient), performance, and ratio of effective therapy time to total session duration during supervised, minimally supervised, and unsupervised therapy. The same tests will be used to compare the answers to the VAS-smiles, a 5-point VAS represented by different emoticons, performed at the end of each therapy session during the 3 phases. For these comparisons, we expect therapy content and VAS-smiles not to vary significantly depending on the level of supervision, as ideally the absence of the therapist should not impact these outcomes. Patients who did not reach the unsupervised phase will be excluded from this analysis.

Linear mixed-effects models will be used to investigate parameters (eg, demographics and baseline data) possibly influencing the achieved dose of unsupervised therapy.

Relevant qualitative data will be summarized and reported accordingly.

Data analysis will be performed with MATLAB R2021b (MathWorks).

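### A shift in exercise mix alone can change repetitions per minute, so the pooled intensity comparison across phases cannot separate a change of exercises from a change of pace

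*Protocol article*

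**What the plan says.** Repetitions enter the protocol article in three places.

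- **Primary Outcomes** lists them as one of three dose metrics: "number of task repetitions (ie, the number of target movements performed". The other two are therapy minutes and the percentage change in physical therapy time.
- **Secondary Outcomes** gives the fuller definition: "A task repetition corresponds to the target action that the patient must perform in a given exercise". The examples that follow are "a movement or combination of movements, such as one opening and closing of the hand or interacting with one virtual object". The same section forms "intensity (ie, number of task repetitions per minute" and says that the difference between phases "is used to evaluate if the content of the therapy varies when the therapist is no longer present".
- **Data Analysis** will "compare intensity (average block intensity for each patient), performance, and ratio of effective therapy time to total session duration" over the three phases, by repeated measures ANOVA or the Friedman test. It adds that "we expect therapy content and VAS-smiles not to vary significantly depending on the level of supervision".

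On the exercises themselves, the Intervention section says that they are assigned to participants. It also says that in the unsupervised phase patients decide when and how much to train. The section on the ReHapticKnob says that algorithms adapt therapy to the individual. The article does not say that the mix of exercises is held constant across phases, nor that intensity is stratified or standardised by exercise.

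**The concern.** If one exercise counts a single hand opening and closing as a repetition and another counts a longer combined action, the two counts are not in the same unit. An average over blocks of both kinds is weighted by how much of each was done. A patient who spends more time on short-action exercises in weeks 3 and 4 then shows a higher intensity without working any faster. One who slows down can show no change if the mix shifts the other way.

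The plan reads this comparison as evidence on what happens when the therapist is absent, and it expects no significant difference. Both errors are therefore possible: an apparent change in pace that is only a change of exercises, and an apparent confirmation that conceals a real slowing. The phases also run in the same order for every patient, so any progression in the exercises would coincide with the withdrawal of supervision.

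**Working it through.** The plan gives no figure on this point to reproduce. It states no movements per repetition, no rate per exercise and no exercise mix. The check is therefore an identity with assumed values.

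**Inputs**
- *m*, movement pace: assumed 6 movements per minute, held constant.
- *T*, time: 45 minutes, from the session length of about 45 minutes in the Intervention section, treated here as all effective time.
- *s*, share of time in exercise A, which has 1 movement per repetition: assumed 50%, then 70% or 30%.
- *k*, movements per repetition in exercise B: assumed 1, 1.5, 2 or 3.

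**Formula**

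Repetitions per minute = m × (s + (1 − s)/k). Total movements = m × T = 6 × 45 = 270 in every case.

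| k | s = 30% | s = 50% | s = 70% | 50% to 70% | 50% to 30% |
|---|---|---|---|---|---|
| 1 | 6.0/min | 6.0/min | 6.0/min | 0% | 0% |
| 1.5 | 4.6/min | 5.0/min | 5.4/min | +8.0% | −8.0% |
| 2 | 3.9/min | 4.5/min | 5.1/min | +13.3% | −13.3% |
| 3 | 3.2/min | 4.0/min | 4.8/min | +20.0% | −20.0% |

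For k = 3 and s = 70%: 6 × (0.7 + 0.3/3) = 6 × 0.8 = 4.8. Over 45 minutes the k = 3 row gives 144, 180 and 216 repetitions for the same 270 movements. The percentages do not depend on m or T.

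**Masking.** Suppose the mix moves from 50% to 70% and pooled intensity stays the same. The pace must then have fallen:
- k = 1.5: 5.0/0.9 = 5.56, a fall of 7.4% from 6.
- k = 2: 4.5/0.85 = 5.29, a fall of 11.8%.
- k = 3: 4.0/0.8 = 5.00, a fall of 16.7%.

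**Does averaging over blocks help?** No, not by itself. If blocks are of equal length and each holds one exercise, the mean block intensity is s × m + (1 − s) × m/k, which is the formula above.

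**Within exercise.** Exercise A gives m and exercise B gives m/k, whatever the mix. Standardised to a fixed 50/50 mix, the result is 5.0, 4.5 and 4.0 per minute for k = 1.5, 2 and 3 at every s, so the mix effect is 0%.

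**The case against.** Much of the case on the other side stands.

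- **No exercise list is given.** A reader might infer that every exercise has a different unit. The text shows only that the unit is tied to the exercise and can differ. With equal units the effect is zero.
- **A shift of mix is not shown.** The only adaptation that the ReHapticKnob section spells out concerns difficulty, and the same assigned exercises may carry through all phases. What can be said is that constancy is not stated, while therapy is personalised and unsupervised training is free.
- **The two definitions are not in sharp conflict.** The one under Primary Outcomes reads as a loose gloss on the fuller one. It needs aligning, no more.
- **Exercise mix is part of therapy content.** Doing different exercises without a therapist is a change that the authors would want to see. This is a reason to keep the pooled measure, but that measure alone cannot say which kind of change occurred. Task performance and the effective-time ratio are read beside it, but neither measures the mix.
- **Detail may sit elsewhere.** A block is not defined, and pooling over exercises is implied rather than stated. A full protocol or analysis plan may handle it. The published text nevertheless fixes an exercise-dependent unit, a single average per patient and the interpretation placed on it.

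A reader might also infer that the dose models rank patients by their exercises, or that minutes should become the lead dose measure. The documents support neither. Data Analysis names no dose metric for the mixed-effects models, and minutes already stand as a separate primary dose metric.

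**Conclusion.** The concern holds in a limited form. By the article's own definition, movement and time per repetition can differ between exercises. The planned phase comparison of one average intensity per patient then cannot separate a change of exercises from a change of pace. The size is unknown from the documents. For a 20-point shift in time share it is 0% with equal units and about 8% to 20% in either direction if movements per repetition differ by a factor of 1.5 to 3. The factor, the shift and the two-exercise setting are all assumptions.

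What is at stake is the reading of a secondary outcome and, to a lesser degree, of the repetition count among the primary dose metrics. Therapy minutes, the percentage change in therapy time and the feasibility measures (transition, attendance, safety) are untouched. It would go too far to say that the intensity results are biased, because the documents do not show that the mix changes.

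**What to change.** 1. Use one definition of a repetition in Primary Outcomes and Secondary Outcomes. The exercise-based one is the fuller.
2. Keep the pooled intensity comparison, and add one within exercise, or standardised to a fixed exercise mix per patient, using exercises performed in all the phases compared.
3. Report the exercise mix by phase, and total repetitions by exercise.

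No change of lead dose measure is needed.

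The cost is a little more analysis. Table 1 lists repetitions, session and break durations and exercise difficulty among the robot's recorded data, and the Results section says that analysis was still under way. This assumes that the log identifies the exercise behind each repetition. The downside is that exercises not performed in every compared phase drop out of the standardised comparison, which is a further reason to keep the pooled one beside it.

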**Figure 2 figure2:**
[figure not shown]
Design of the interventional study for each of the study participants. All participants undergo a screening visit, baseline assessments, 1 week of supervised therapy, and 1 week of minimally supervised therapy. After the first week of minimally supervised therapy, the therapist checks whether the patient properly learned how to use the technology and is ready for unsupervised training. If yes, the patient proceeds to 2 weeks of unsupervised use. If no, an additional week of minimally supervised therapy is performed. At the end of this second week, the therapist checks again whether the patient can train independently. If yes, the patient proceeds to 1 week of unsupervised therapy. If no, an additional week of minimally supervised therapy is performed. In total, each patient performs 4 weeks of technology-assisted rehabilitation. At the end of the protocol, the clinical and robotic assessments as well as the evaluation of the user experience and usability are repeated for all patients.

**Table 1 table1:** Data collected and procedures (marked with an “X”) performed at each time point of the clinical trial, with primary (PO) and secondary (SO) outcomes indicated. Day 0 corresponds to the first supervised robot-assisted therapy session. The time range indicates how far a procedure can be advanced (–) or postponed (+) for organizational reasons from the precise time point at which it should be performed.

		Screening visit	Baseline clinical assessment	Baseline robotic assessment	Robot-assisted therapy sessions		Usability evaluation 1	Robot-assisted therapy sessions		Final clinical assessment	Final robotic assessment	Usability evaluation 2
Time point		Day –2	Day –1	Day –1	Day 0-6	Day 7-13	Day 13	Day 14-20	Day 21-27	Day 27	Day 27	Day 27
Time range (days)		–4 to +1	±2	±1	—^a^	—	±2	—	—	±2	±2	±2

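### Functional recovery, a change score completed only as the unsupervised dose ends, is listed as a possible influence on that dose, so an association could be read in the wrong direction

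*Protocol article*

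**What the plan says.** The Secondary Outcomes section introduces a set of explanatory variables with the words "Other parameters possibly influencing therapy dose or attendance are also evaluated" and then names them: "These comprise age, baseline assessment scores, functional recovery, the number of total conventional therapy sessions, and functional independence and mobility". The last item is measured with the Barthel index and custom questions each time the checklist is completed.

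The same section defines the third item: "Functional recovery, assessed as the difference between the baseline and final scores in the clinical and robotic assessments". There are five clinical scores (Fugl-Meyer upper extremity, ABILHAND, Box and Block, MESUPES, modified Ashworth) and three robotic ones: "Robotic assessments comprise active range of motion, hand proprioception, and haptic perception".

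On timing, the Figure 2 caption says: "At the end of the protocol, the clinical and robotic assessments as well as the evaluation of the user experience and usability are repeated". Table 1 places these final assessments at Day 27 (±2), the baseline ones at Day –1, and unsupervised therapy on Days 14 to 27. A patient who needs one extra minimally supervised week starts the unsupervised phase a week later.

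The Data Analysis section says: "Linear mixed-effects models will be used to investigate parameters (eg, demographics and baseline data) possibly influencing the achieved dose of unsupervised therapy". The Intervention section adds that recovery will not be used to judge efficacy, but to relate impairment profiles to the increase in dose. The Introduction presents dose as a major contributor to sensorimotor recovery.

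**The concern.** A variable offered as an influence on dose should be fixed before the dose is given. Here the final half of the change score is observed when the dose has essentially been delivered. By the article's own rationale, recovery is partly a product of dose. If patients who train more also recover more, an analysis with dose as the response and recovery as a predictor will show an association. Under the stated heading, that association would be presented as recovery influencing dose.

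At stake is the second half of the secondary objective in the Introduction: which patient characteristics affect how much therapy patients give themselves. A smaller, related worry is the length of the candidate list relative to the number of patients, because chance findings become easy.

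**Working it through.** **Sample size.** The Sample Size section needs 10 patients and allows for about 20% dropout: 10 / (1 – 0.20) = 12.5, rounded up to 13. This reproduces the stated 13. The Results section reports 13 completers. The article does not say how many of them reached the unsupervised phase, so 13 is a ceiling for any analysis of unsupervised dose.

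**Timing.**
- The change score spans Day –1 to Day 27, which is 28 days.
- If unsupervised therapy starts on Day 14, 15 of the 28 days (54%) precede it and 13 overlap with it. If it starts on Day 21, 22 days (79%) precede it.
- Table 1 schedules none of the eight clinical and robotic assessments between baseline and the final visit. The change score therefore cannot be split into a part before the dose and a part during it.

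**Size of the direction problem.** Assume that dose drives recovery with correlation r, that recovery has no effect on dose, and that a two-sided 5% test is used (the article states no level).
- Critical correlation at n = 13: t / √(n – 2 + t²) with t = 2.201 on 11 df, so 2.201 / √(11 + 4.844) = 0.553.
- Simulation (40,000 trials per setting; recovery = r × dose + √(1 – r²) × noise) gives the share of trials in which recovery is a significant predictor of dose:

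| assumed r | n = 13 | n = 10 |
|---|---|---|
| 0 | 5% | 5% |
| 0.3 | 16.7% | 13.4% |
| 0.5 | 42.9% | 32.5% |
| 0.7 | 81.6% | 67.7% |

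- Cross-check by the Fisher approximation, Φ(atanh(r) × √(n – 3) – 1.96) at n = 13: 16%, 41% and 78% for r = 0.3, 0.5 and 0.7.

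**Secondary point: number of candidates.**
- Count from Secondary Outcomes: age 1 + baseline scores (5 + 3) + change scores (5 + 3) + conventional sessions 1 + Barthel 1 = 19, before the custom questions. Without recovery, 19 – 8 = 11.
- If each were tested singly at 5% for one dose metric, with no true effects and independent candidates: 1 – 0.95^19 = 62%; for 11, 1 – 0.95^11 = 43%.
- The candidates will be correlated. Simulation at n = 13 (20,000 runs) with common pairwise correlation 0.3, 0.5 and 0.7 gives 54%, 44% and 31% for 19 candidates, and 39%, 32% and 24% for 11.
- Primary Outcomes names three dose metrics, so these figures apply to each.

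**The case against.** **Recovery may not be in the model.** The Data Analysis section gives demographics and baseline data as examples and does not name recovery. A reader might infer that the mixed model certainly contains it, but the article does not say so. The link rests on the shared idea of parameters influencing dose and on the Intervention section's statement about how recovery is used. This stands as a limit on the claim. It does not remove the point, because Secondary Outcomes gives recovery the role of an influence whatever the model.

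**Recovery could affect dose.** A reader might conclude that recovery cannot influence dose at all. That is too strong: more than half of the change interval precedes Day 14, and a patient who improves early may well train more. What remains is that the change score cannot tell this from the reverse.

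**The multiplicity argument leans on detail the article may leave to the full plan.** This largely stands. The article does not say that all 19 candidates are tested, sets no significance level for these models, and does not say that they are fitted together. A reader might infer one joint model, which would leave 13 – 1 – 19 = –7 between-patient degrees of freedom, but no such model is described. The 62% also needs independent candidates, which change scores computed from the baseline scores are not.

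**Not every candidate is strictly constant within a patient.** Barthel and the custom questions are repeated for patients who need extra minimally supervised weeks, and conventional therapy is recorded in every therapy week. The ceiling of 13 applies fully to age, baseline scores and change scores, which are 17 of the 19.

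**The consequences are limited.** A reader might suppose that these predictors will select patients for the next study. The article does not say that. The examples under the secondary objective are age, cognition and impairment, and no primary outcome depends on this analysis.

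**Conclusion.** The point holds in a limited form. Secondary Outcomes assigns the role of possible influence on dose to a change score that is complete only at about Day 27, when the dose of Days 14 to 27 has essentially accrued. The article's own rationale runs from dose to recovery, and no intermediate assessment can separate the two directions. The chance of a significant association that could be misread this way is about 17% to 82% for r between 0.3 and 0.7. Those figures assume 13 analysable patients, a 5% level and no effect of recovery on dose.

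The candidate count is secondary and conditional. The 31% to 62% applies only if all 19 are tested singly at 5% for one dose metric and none has a true effect. It is a reason for cautious presentation, not evidence that false predictors will be reported.

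**What to change.** - In Secondary Outcomes, remove functional recovery from the parameters said to influence dose or attendance. If it was to enter the mixed models in Data Analysis, remove it there too.
- Limit predictors of dose to variables measured before the unsupervised phase. The total of conventional sessions accrues during the study, so count only sessions before that phase or leave it out. Leaving it out gives 10 candidates (1 – 0.95^10 = 40% if independent; 36% to 23% at correlation 0.3 to 0.7).
- Report the relation between dose and recovery separately, as a descriptive association with baseline-adjusted change and without a claim about direction.
- Show predictor results as estimates with confidence intervals, using patient-level degrees of freedom for patient-level variables however many sessions are recorded, and label them hypothesis-generating. Removing recovery alone does not settle the multiplicity question, so this label is needed as well.

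The cost is a change of wording in the analysis; no new data are needed, and the article describes the analysis as still in progress. The downside is that fewer predictors can be reported as tested.
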